# Brain activity and upper limb movement analysis in children with Down syndrome undergoing transcranial direct current stimulation combined with virtual reality training: study protocol for a randomized controlled trial

**DOI:** 10.1186/s13063-022-06014-4

**Published:** 2022-01-28

**Keywords:** Down Syndrome, Brain Activity, Virtual Reality, Transcranial Direct Current Stimulation, Upper Limb Movement

## Abstract

**Background:**

Children with Down syndrome have poorer functional and sensory skills compared to children with typical development. Virtual reality (VR) training could help improve these skills. Moreover, transcranial direct current stimulation (tDCS) has achieved promising results in terms of enhancing the effects of physical and sensory therapy by modulating cortical excitability.

**Methods/design:**

Two investigations are proposed: (1) an observational study with a convenience sample consisting of children with Down syndrome (group 1—cognitive age of 6 to 12 years according to the Wechsler Abbreviated Scale of Intelligence) and children with typical development 6 to 12 years of age (group 2). Both groups will undergo evaluations on a single day involving a three-dimensional analysis of upper limb movements, an analysis of muscle activity of the biceps and brachial triceps muscles and an analysis of visuospatial and cognitive-motor variables. (2) Analysis of clinical intervention: a pilot study and clinical trial will be conducted involving individuals with Down syndrome (cognitive age of 6 to 12 years according to the Wechsler Abbreviated Scale of Intelligence). The sample will be defined after conducting a pilot study with the same methodology as that to be used in the main study. The participants will be randomly allocated to two groups: An experimental group submitted to anodal tDCS combined with a VR game and a manual motor task and a control group submitted to sham tDCS combined with a VR game and a manual motor task. The training protocol will involve 10 sessions of active or sham tDCS during memory and motor task games. Three 20-min sessions will be held per week for a total of 10 sessions. Evaluations will be performed on three different occasions: pre-intervention, post-intervention (after 10 sessions) and follow-up (1 month after the intervention). Evaluations will consist of analyses of electroencephalographic signals, electromyographic signals of the biceps and triceps brachii, and the three-dimensional reconstruction of the reaching movement. The results will be analyzed statistically with the significance level set at 5% (*p* ≤ 0.05).

**Discussion:**

The optimization of the results obtained with virtual reality training is believed to be related to the interactive experience with a wide range of activities and scenarios involving multiple sensory channels and the creation of exercises, the intensity of which can be adjusted to the needs of children. Therefore, the proposed study aims to complement the literature with further information on tDCS and VR training considering different variables to provide the scientific community with clinical data on this combination of interventions.

**Trial registration:**

Brazilian Clinical Trials Registry (REBEC) protocol number RBR-43pk59 registered on 2019 March 27 https://ensaiosclinicos.gov.br/rg/RBR-43pk59 and Human Research Ethics Committee number 3.608.521 approved on 2019 September 30. Protocol version 2021 October 20. Any changes to the protocol will be reported to the committees and approved. Informed consent will be obtained from all participants by the clinical research coordinator and principal investigator.

**Supplementary Information:**

The online version contains supplementary material available at 10.1186/s13063-022-06014-4.

## Background

Down Syndrome (DS) is a genetic condition that receives the code Q–90 in the International Classification of Diseases (ICD-10). DS is considered one of the most frequent numerical autosomal chromosome anomalies and is recognized as a major cause of mental disability [1, 2]. Affected individuals have a variety of learning and developmental problems, which exert a direct impact on selective motor control, compromising the acquisition of motor skills and functional independence [3–5].

The literature describes several morphofunctional characteristics that affect the motor system in children with DS, such as muscle hypotonia (99%), broad hands and short fingers (70%), joint hyperextension (80%), and ligament laxity, which is correlated with joint instability. These problems are related to delayed motor development and muscle diastasis, which hinder the performance of precise movements [5]. Although these characteristics are not fully understood in the literature, children with DS are known to have structural and functional brain abnormalities in the early stages of development, with deficiencies in both gray and white matter, reduced myelinization as well as presynaptic and synaptic disorders [5]. These problems may influence the initial development of brain circuits, affecting the installation and consolidation of the neural network connections necessary to establish the mechanisms of attention, memory, correlation and abstract thinking [6, 7].

The magnitude of motor and cognitive deficits in this population varies throughout development [8] and can interfere with the ability to perform routine functions and tasks in an independent manner [9–12]. Thus, novel rehabilitation techniques have been studied with the aim of minimizing the dysfunctions that affect this population. The results of clinical studies involving transcranial direct current stimulation show the considerable potential of this stimulation method in the treatment of neurological disorders [6, 7, 13–16] by modulating the excitability of the central nervous system [17, 18].

Transcranial direct current stimulation (tDCS) is a relatively low-cost technique that is easy to apply, has minimal side effects and is capable of inducing lasting changes in the excitability of the motor cortex [17]. Greater benefits are seen when this technique is combined with a motor task. According to the literature, tDCS promotes changes in the dysfunctional excitability pattern, enabling motor training to mold the functional pattern of cortical activity [18] by activating task-specific neural networks, thereby optimizing the functional outcome due to the enhancement of neuroplasticity [18–21].

Virtual reality (VR) stands out among the most widely used motor training methods in the literature [22] .Rehabilitation-oriented VR games have gained prominence by enabling greater interactivity and immersion into the rehabilitation process compared to conventional treatments. Games create alternative scenarios, encouraging the practice of physical activity that might otherwise be considered tedious and tiresome [22–26].

Although the use of VR therapies for the treatment of movement dysfunctions in children with DS has been studied in the academic community, there remains a lack of scientific material on the subject [27, 28]. However, studies involving the use of VR for upper limb training in children with cerebral palsy have shown promising results, such as improved sensorimotor and adaptive information [29]. VR as an auxiliary instrument in physical therapy offers a motivational, playful manner to facilitate the development of sensory and motor skills, favoring the active participation of the individual, the training of planning skills, motor control, and the development of strategies for overcoming motor challenges.

This will be the first study to correlate variables and evaluate the effects of anodal tDCS combined with physical therapy involving a VR game in children with DS. For such, it is necessary to employ evaluative methods that can determine the effects of this combined therapy on the population with DS. For a complete evaluation of motor adaptation and the effects of the proposed intervention, electromyographic signals, electroencephalographic signals, and movement kinematics will be obtained during a manual reaching task motivated by a VR game.

## Objective/hypotheses

The objective of the study is to perform a comparative analysis of brain activity, muscle activity and upper limb kinematics during the execution of a manual motor task motivated by a VR game during anodal tDCS in children with DS. Psychomotor, muscle, and cognitive skills will be assessed before and after the intervention as well as at the 1-month follow-up. The objectives of the study will be to (I) correlate variables related to movement kinematics, motor activity, and brain activity, (II) compare the effects of transcranial stimulation in children with DS and those with typical development (TD), (III) determine the effects and possible adverse effects of anodal tDCS at an intensity of 1 mA administered during 20 min of training in children with DS, and (IV) determine the effects of different anodal tDCS montages in children with DS.

The null hypothesis of the study is that the results of ten sessions of anodal tDCS over the F3 region of the cortex during a motor task motivated by a VR game will not differ significantly from the results obtained from ten sessions of sham tDCS with the same training in children with DS. The alternative hypothesis is that the results of ten sessions of anodal tDCS over the F3 region of the cortex during a motor task motivated by a VR game will differ significantly from the results obtained from ten sessions of sham tDCS with the same training in children with DS.

## Methods/design

### Study design

This is a protocol study for a randomized controlled clinical trial consisting of three phases (Fig. 1) and written based on the SPIRIT statement (Additional file 1). In phase 1, an exploratory analysis will be performed to identify the parameters of children with DS compared to those with typical development (TD). Phase 2 is a pilot study that will provide information for the calculation of the sample size in phase 3. Phase 3 will be a randomized clinical trial with a comparison between two groups (proportion of 1:1)—a control group (CG) and experimental group (EG), expecting superiority in the EG. The time schedule of the trial enrollment, interventions, assessments, and visits of participants is displayed in Table 1.

**Fig. 1 Fig1:**
[figure not shown]
Flowchart of phases in accordance with CONSORT statement. DS, Down syndrome; TD, typical development; tDCS, transcranial direct current stimulation; VR, virtual reality

**Table 1 Tab1:** Time schedule of trial enrollment, interventions, assessments, and visits of participants

Timepoint	Enrolment	Allocation	Intervention		End-line	Follow-up 1 post 10 session	Follow-up 2 1-month post 10 session
	Month 0-1	Month 1	Month 2–5	Month 5–8	Month 8	Month 8–10	Month 11–13
**Enrolment**							
Eligibility screen	X						
Informed consent	X						
Allocation		X					
**Studies**							
**Study 1:**							
Group 1: Evaluation of 12 individuals with DS.			X				
Group 2: Evaluation of 12 normal individuals			X				
**Intervention**							
**Study 2:**							
Active tDCS + VR pilot				X			
Sham tDCS+ VR pilot				X			
(G1) Active tDCS + VR				X			
(G2) sham tDCS + VR				X			
**Assessments**							
Anthropometric data	X						
WASI: cognitive age data	X						
**Physiological measures**							
Electroencephalographic analysis	X				X	X	X
Surface electromyography (EMG)	X				X	X	X
Three-dimensional motion analysis	X				X	X	X

This study will investigate normality patterns in upper limb movements in typical children and determine patterns in children diagnosed with DS to enable the establishment of effective interventions to improve motor skills in this population.

### Study setting

The study will be carried out at two locations: (1) School of Medical Sciences of Santa Casa de São Paulo and (2) Integrated Laboratory of Movement Analysis at UniEvangélica - Centro Universitário de Anápolis. These environments will offer the necessary infrastructure for recruiting participants (children with DS and children with DT) and data acquisition as well as sufficient institutional support to ensure the execution of the project. The Integrated Movement Analysis Laboratory is based at the University Center of Anápolis- UniEvangélica. The researchers are fully committed to the rapid, multifaceted dissemination of study results, regardless of the findings. The results will be presented to the head of the Movement Analysis Laboratory and community parties. The data will also be made available in local and international submissions for publication.

### Eligibility criteria

#### Sample selection and characterization of healthy children

Children with typical development will be recruited from a database at the university.

Inclusion criteria:
No diagnosis of cognitive and/or neuromotor disorders;Considered neurotypical individual;6 to 12 years of chronological age;Cooperation during procedures;Signed statement of informed consent by legal guardian;Positive manifestation and consent of child to participate.

#### Sample selection and characterization children with DS

The population will be composed of children diagnosed with DS who will be recruited from the outpatient clinic of the University Center of Anápolis and the Association of Parents and Friends of Exceptional Children of Anápolis, which is a partner institution of the university. Inclusion criteria:
Diagnosis of DS;Ability to understand procedures involved in study;Adequate cooperation;Cognitive age between 6 and 12 years defined by Wechsler Abbreviated Scale of Intelligence (WASI);Signed statement of informed consent by legal guardian;Positive manifestation and consent of child to participate.

### Evaluation of cognitive age

All children with DS will be assessed with regards to cognitive age using the Wechsler Abbreviated Scale of Intelligence (WASI), which is a tool designed to assess intellectual performance. This scale was developed from the Wechsler Intelligence Scale and the revised scale for children to meet the demand for a short, reliable intelligence measure that could be used in clinical, psychoeducational and research settings while maintaining the possibility of interpreting a unified instrument. The evaluation using this scale will be performed by the psychologist in charge of the cognitive analysis.

Exclusion criteria:
Having undergone surgical procedures that can alter biomechanics in 12 months prior to onset of training sessions;Orthopedic deformities of upper limbs or spine with indication for surgery;Diagnosis of uncontrolled epilepsy;Metal implants in skull or hearing aids;Other neurological disorder besides DS;Use of pacemaker.

The participants and legal guardians will receive the screening results and counseling on clinical management as indicated. Eligible participants will receive a follow-up appointment at the clinic to conduct the enrollment procedures.

### Ethical aspects

The present study complies with the norms governing research involving human subjects stipulated by the Brazilian National Board of Health in October 1996 and updated in Resolution 466 in 2012 as well as the precepts delineated in the Declaration of Helsinki. The study received approval from the Research Ethics Committee of the School of Medical Sciences of the Santa Casa de São Paulo (certificate number: 3.608.521) and was registered with the Brazilian Registry of Clinical Trials (REBEC protocol number RBR-43pk59 registered on 2019/03/27). The authors confirm that all ongoing and related trials for this intervention are registered. All participants and their legal guardians will agree to participate in the study by signing a statement of informed consent (Appendix A) and Minor Consent Form (Appendix B). The consent form is available in the local language. The participants and their guardians will have the opportunity to ask questions about participation in the study. Once a participant and guardian agree to participate, the study team will obtain written consent. Written permission will be obtained from the legal guardians and consent to participate will be obtained from the participants.

The participants will be allowed to abandon the study at any time with no negative consequences. Absolute confidentiality regarding the identification of children will be assured. The participants will be informed of the existence of a sham group prior to the start of the survey. The sham intervention procedures will always be performed in combination with active (VR training), reducing the impact on the patient. No biological material will be collected. The participants will provide consent separately for the use of images but will be assured that their identity will be maintained confidential in all stages of the study.

In studies 2 and 3, the participants will receive an intervention scheme with active or sham tDCS. Depending on the results, a protocol will be used at the end of the study so that everyone receives the active intervention to ensure that all participants benefit during the study.

### Sample size

A convenience sample will be used in phase 1, which will be an exploratory analysis to identify and compare the profile and motor variables of children with DS and TD. Phase 2 will be a pilot study with a random, exploratory sample using the formula of Student’s *t*-test with a minimum power of 80% (power equal to type II error) and 5% significance level (power equal to type I error) to furnish the calculation of the sample size for phase 3. Phase 3 will be a randomized controlled clinical trial with the sample size based on the findings of phase 2.

### Randomization

A randomization in blocks will be applied. The participants will be randomly allocated to one of the two groups: group 1—anodal tDCS (anodal electrode positioned over the F3 region of the cortex following the international electroencephalogram 10-20 system and cathode positioned on the deltoid muscle) associated with VR training—and group 2—sham tDCS (anodal electrode positioned over the F3 region of the cortex following the international electroencephalogram 10-20 system and cathode positioned on the deltoid muscle) associated with VR training. Randomization will be performed at the website www.random.org and conducted by a person blind to the objectives and protocol of this study.

### Group allocation

The allocation of the participants will be concealed in sequentially numbered, sealed, opaque envelopes prepared prior to the study by a research assistant who will not be involved in the study. After the baseline measures have been collected, participants will be randomly assigned to the experimental or control group by the treating therapist, who will open the envelopes and read the contents. All outcomes will be measured by blinded assessors. All enrolled participants will receive a code to protect confidentiality before, during, and after the trial.

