## Statistical analysis of results

Statistical analysis will involve the calculation of mean, standard deviation, minimum and maximum values for the descriptive analysis of the effects of tDCS and VR on the quantitative variables. The Shapiro-Wilk normality test will be used to determine the distribution of the data in terms of adherence to the Gaussian curve. Parametric variables will be expressed as mean and standard deviation. Nonparametric variables will be expressed as median and interquartile range.

For phase 1, either Student’s *t*-test or Mann-Whitney test will be used to compare quantitative variables between the TD and DS groups. In phase 2, descriptive measures of mean and standard deviation will be used as initial values for the calculation of the sample size in phase 3. In phase 3, we will analyze quantitative variables with measures over time (pre-intervention, post-intervention and one-month follow-up) and comparisons of the EG and CG will be performed using repeated-measures ANOVA. The level of significance will be set at 5% for all statistical tests. The data will be organized, tabulated and analyzed with the aid of the Statistical Package for the Social Sciences (v.25.0).

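### Table 1 places the pre-intervention EEG, EMG and motion recording, and the allocation, at least four months before the first stimulation session

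*Protocol article*

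**What the plan says.** The protocol article describes the assessment plan in words and in a dated table.

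- **Abstract, Methods/design:** "Evaluations will be performed on three different occasions: pre-intervention, post-intervention (after 10 sessions) and follow-up (1 month after the intervention". The course is also defined there: "Three 20-min sessions will be held per week for a total of 10 sessions".
- **Group allocation:** "After the baseline measures have been collected, participants will be randomly assigned to the experimental or control group".
- **Statistical analysis of results:** phase 3 analyses "measures over time (pre-intervention, post-intervention and one-month follow-up"), and "comparisons of the EG and CG will be performed using repeated-measures ANOVA".
- **Study design, Table 1:** its title is "Time schedule of trial enrollment, interventions, assessments, and visits of participants". The rows for EEG, surface EMG and three-dimensional motion are marked at Enrolment (Month 0–1), End-line (Month 8), Follow-up 1 (Month 8–10) and Follow-up 2 (Month 11–13). Allocation is marked at Month 1. The four tDCS + VR rows (pilot active, pilot sham, trial active, trial sham) are marked only in the second Intervention column, Month 5–8.

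The Evaluation process section repeats the three occasions (before, after and one month later). It gives no date for the first one and no repeat baseline.

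**The concern.** The text treats the first recording as the level immediately before a short course of treatment. The table puts it, and the randomisation, months earlier. Three things follow if the schedule is carried out as printed.

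- **Interpretation of change.** The participants are children, and the Intervention protocol section accepts that they may need rehabilitation outside the study. A pre-to-post change would then contain months of development and other therapy as well as the three-week intervention. The Secondary results section asks whether the movement, muscle and brain parameters can be modified by the protocol, and within-arm change would be a poor guide to that.
- **Precision.** The repeated-measures analysis uses the baseline as one of its occasions. An older baseline is likely to correlate less with the post-treatment value.
- **Attrition.** A child who withdraws while waiting has already been randomised and counts as a post-randomisation loss, although no session was given.

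**Working it through.** **Inputs**, all from the protocol article, with Table 1 read by column position:

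- Enrolment window, the only pre-treatment column marked for EEG, EMG and motion: Month 0 to 1.
- Allocation: Month 1.
- Treatment window for every tDCS + VR row: Month 5 to 8.
- First post-treatment mark: End-line, Month 8.
- Course: 10 sessions at three per week.

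The plan states no figure for the interval between baseline and first session, so there is none to reproduce.

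**Length of the course.** Three weeks hold 9 sessions. The tenth opens the fourth week, 21 days after the first: 21 / 30.44 = 0.69 month.

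**Baseline to first session.**

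- Shortest: start of treatment window minus end of enrolment window = 5 − 1 = 4 months.
- Longest: the latest first session that lets the course finish by Month 8 is 8 − 0.69 = 7.31. Minus the start of enrolment: 7.31 − 0 = about 7.3 months.

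**Allocation to first session.** 5 − 1 = 4 months to 7.31 − 1 = about 6.3 months.

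**Baseline to End-line.** 8 − 1 = 7 months to 8 − 0 = 8 months, against a course of about 0.7 month.

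**Does the reading of the month headings matter?** If they are a clock for each child, the gaps are as above. If they are a project calendar, enrolment and allocation still close by Month 1 and treatment still opens at Month 5, so the last child enrolled and the first treated are still 4 months apart. Rolling entry would need enrolment to run beyond Month 1, which the table does not show.

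**Effect on the comparison between arms.** In each arm the expected change is a time effect (development, outside therapy, VR training) plus, in the active arm, any effect of stimulation. Baseline is taken before randomisation and both arms wait equally, so the time effect cancels in expectation when the arms are compared. It does not cancel in the change within one arm.

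**Effect on precision.** With equal variances σ² and baseline-post correlation ρ, the variance of the change is 2σ²(1 − ρ), which rises as ρ falls. The document gives neither ρ nor its decline over time, so the direction can be argued but the size cannot be computed.

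**The case against.** Several objections have force.

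**The physiological rows do not list every recording.** Table 1 marks the Study 1 evaluations of 12 children with Down syndrome and 12 typically developing children in Month 2–5, yet the EEG, EMG and motion rows have no mark there. A reader might infer from those rows that nothing is measured in either Intervention column. That is not so, and a missing mark does not prove that no later recording is made. But Study 1 is a single-day cross-sectional comparison, and nothing makes it the baseline of the intervention studies. A Month 2–5 recording would also fall after the Month 1 allocation, against the order in the Group allocation section.

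**The calendar itself is unreliable.** Pilot and trial share Month 5–8 and one allocation date, although the Sample size section bases the trial's size on the pilot. The visit labelled one month after the sessions sits at Month 11–13, at least 11 − 8 = 3 months after treatment closes. Four physiological assessments are marked against three in the text. So the lag may be a scheduling error and not an intention. This stands, and it is a reason to correct the conflicts together. It does not dispose of the point: re-dating phase 3 would not by itself tie the baseline recording to the first session.

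**The sham control protects the hypothesis.** A reader might infer that an old baseline biases active against sham. It does not, for the reason given in the working.

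**No power loss can be quoted.** A reader might wish to put a figure on lost power. That would need assumed correlations and a fixed sample size. Neither exists: phase 3 is sized from a pilot using the same methods. If the sizing rests on the variability of change, a similar lag in the pilot would already be reflected in it. If it rests on post-treatment means alone, the correlation does not enter.

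**Dropout is already allowed for.** The 20% increase under Study 2 covers numbers. It does not alter the fact that a child lost while waiting is lost after randomisation.

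**Conclusion.** The point holds as a scheduling defect that should be corrected. As printed, the baseline for the intervention studies is 4 to about 7.3 months old at the first session, and children are randomised 4 to about 6.3 months before it, for a course of about 0.7 month. These figures assume that Table 1's month headings are meant as printed, that its marks are aligned as read, and that the course finishes by Month 8.

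The consequences are a pre-to-post change that cannot be attributed to the intervention within an arm, a probable but unquantified loss of precision, and avoidable post-randomisation losses. The randomised comparison remains valid in expectation. The sentence in the Group allocation section is sound in itself. The fault lies in Table 1 set against the label of the first assessment. Whether the lag is intended cannot be settled from the document, but on either reading the timing of the baseline needs to be stated.

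**What to change.** In Table 1:

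- Keep eligibility screening, consent, WASI and anthropometry at Enrolment.
- Move the EEG, EMG and 3D motion marks to a new Pre-intervention column shortly before the first stimulation session, within a window that the sponsor states.
- Place Allocation directly after that column.
- Do this separately for the pilot and the trial, and reconcile in the same revision the shared pilot and trial window, the month of the one-month follow-up, and the number of post-treatment assessments.

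In Group allocation and Evaluation process, say that this recording is the baseline, so that it is the pre-intervention value in Statistical analysis of results.

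If children have already been enrolled under the printed schedule, report by arm the interval from baseline recording to first session and the number lost between allocation and first session.

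The cost is a revision of the table and a few sentences. The recording is moved, not added, so no extra visit is needed. If an enrolment recording is kept as well, it adds one assessment of at most 1 h 30 min per child, the maximum given under Evaluation process.
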